## Abstract

**Background:**

In many countries exercise prescriptions are used in an attempt to initiate a physically active lifestyle in sedentary populations. Previous studies have primarily evaluated low intensive exercise prescription interventions and found moderately positive effects on physical activity and aerobic fitness. In a highly intensive Danish exercise prescription scheme called 'Exercise on Prescription' (EoP) the general practitioners can prescribe EoP to sedentary patients with lifestyle diseases. The aim of this randomized trial is to assess the short- and long-term effects of the EoP scheme. Thus, the aim of this paper is to describe the randomized controlled trial designed for evaluating effectiveness of EoP, and to present results from validations of outcome measures.

**Methods/Design:**

EoP involves a 16-week supervised training intervention and five counselling sessions (health profiles). All patients referred to EoP were eligible for the trial and were offered participation during the baseline health profile. Comparisons between the EoP group and the control group were made at baseline, and after four and ten months. Physiological measures used were maximal oxygen uptake (VO_2_max), glycosylated haemoglobin (HbA1c), bodyweight, and BMI. Patient-reported measures used were physical activity, health-related quality of life, amount and intensity of exercise, compliance with national guidelines for physical activity, and physical fitness. The validation of the cycle ergometer test found a strong correlation between maximal work capacity and VO_2_max, and acceptable test-retest reliability at group level. Calibration of the HbA1c apparatus was stable over ten weeks with minimal use, and test-retest reliability was good. High agreement percents were found for test-retest reliability for the self-administered questionnaire.

**Discussion:**

The trial is designed to provide information about the effectiveness of the EoP scheme. The trial is part of a health technology assessment of EoP, which besides the effectiveness covers the patient perspective, the organization, and the health economy. All three methods validated were found useful for the EoP trial.

## Background

Epidemiological studies have reported a reduced risk of lifestyle diseases and/or mortality with increased level of physical activity [1] and aerobic fitness [2]. A physically active lifestyle is recommended both as part of treatment, prevention and rehabilitation with regard to a number of lifestyle diseases [3]. Despite increasing awareness of the benefits of a physically active lifestyle, large parts of the population remain physically inactive, posing a serious threat to public health [4,5].

In many countries exercise prescriptions are used in an attempt to initiate a physically active lifestyle in sedentary populations. However, a recent population-based analysis questions the impact of exercise prescriptions on increased physical activity at population level [6], and a population-based survey reports that general practitioners (GPs) give physical activity advice and exercise prescription to only 13 % and 3 %, respectively [7]. Furthermore, a recent review concludes that exercise prescriptions only have a moderately positive effect on physical activity level and aerobic fitness [8]. However, exercise prescriptions are still used extensively [9]. Most exercise prescription studies have evaluated GP counselling in combination with low intensive interventions (e.g. possibility to see an exercise specialist [10], pedometers and exercise logs [10], community-based activities and telephone support [11], access to local physical activity facilities and leisure centres [12], telephone booster calls [13], and stage-matched written material [14]). Few studies have evaluated highly intensive exercise prescription interventions [8,15,16], and limited evidence supports the hypothesis that more intensive interventions will lead to larger improvements in physical fitness and physical activity [8,17]. Furthermore, very few studies have used good measures of aerobic fitness and physical activity [18].

In an exercise prescription scheme called 'Exercise on Prescription' (EoP) used in a number of Danish counties GPs can refer sedentary patients with medically controlled lifestyle diseases or risk of developing lifestyle diseases to an EoP programme. EoP is a highly intensive exercise prescription scheme, which is implemented in primary care and includes group-based supervised training and motivational counselling.

The aim of this randomized trial is to assess the short- (four months) and long-term (ten months) effects of the highly intensive EoP scheme on physiological variables (maximal oxygen uptake (VO_2_max), glycosylated hemoglobin (HbA1c, in patients with impaired glucose tolerance), Body Mass Index (BMI), and bodyweight) and patient-reported variables (physical activity, health-related quality of life, amount and intensity of exercise, compliance with national guidelines for physical activity, and physical fitness). Thus, the aim of this paper is to describe the randomized controlled trial designed for evaluating effectiveness of EoP, and to present results from validations of outcome measures.

## Methods/design

The EoP scheme was evaluated in a randomized trial conducted in 2005–2006 with two groups: EoP and control patients. The EoP scheme was launched one year prior to the evaluation and offered by the County of Ribe and the County of Vejle. Patients were referred to the EoP scheme by their GP. GPs act as gatekeepers in the Danish health care system [19].

The motivational counselling and the group-based supervised training intervention in EoP patients were carried out by a physiotherapist in 14 clinics geographically spread throughout the two counties.

### Intervention

Participants randomized to the EoP group followed a supervised group-based training intervention together with 8–12 other EoP patients (including patients not taking part in the trial) (Figure 1). Furthermore, the participants received motivational counselling (health profiles) at baseline and after two, four, seven, and ten months aimed at increasing daily physical activity. The health profiles were also used for making a physical activity plan in collaboration between the physiotherapist and the patient, and the patient was responsible for the execution of the plan. During the first two months two weekly 1-hour training sessions were completed. During the final two months one weekly 1-hour training session was completed, totalling 24 training sessions over four months. The group-based training intervention involved elements of aerobic conditioning (e.g. Nordic walking and aerobics), light strength conditioning (primarily using light weights and high number of repetitions), stretching, and games. The physiotherapists were instructed in focusing on training improving aerobic capacity (more than 50% of heart rate reserve for a minimum of 20 minutes [20]) in the majority of training sessions.

**Figure 1 F1:**
[figure not shown]
Schematic overview of the randomized trial of 'Exercise on Prescription' (EoP). The general practitioner (GP) prescribes EoP for sedentary patients with medically controlled lifestyle diseases. The patient takes the prescription to an EoP clinic. Patients randomized to the EoP group complete five health profiles and a 4-month supervised training intervention. The health profiles are completed at baseline, and after two, four, seven, and ten months. The supervised training is organized in groups of 8–12 EoP patients, and involves many different forms of physical activity. Patients randomized to the control group receive only the counselling at baseline, and after four and ten months. After taking part in the trial the control group is offered EoP.

Participants randomized to the control group were called in for a counselling session following randomization (Figure 1). Furthermore, the control group received similar health profiles as the EoP group, but only after four and ten months. After participating in the evaluation the control group was offered EoP.

### Inclusion and exclusion criteria

General practitioners could refer patients with the following characteristics: 1) medically controlled lifestyle diseases, 2) motivated to change of lifestyle, 3) believed to be able to improve health from an increased physical activity level, and 4) willing to pay 750 DKr. (100 €) for the intervention. In addition to giving the referral the general practitioner informed the patient about the benefits of a physically active lifestyle in general.

### Recruitment and allocation

Referred patients contacted an EoP clinic, and an appointment for the first health profile was scheduled (Figure 1). All patients referred to the EoP scheme were eligible for the trial and were offered participation in the randomized trial during the baseline health profile. Recruitment took place over 14 months in 2005 and 2006.

Informed consent was obtained, and volunteering patients were randomized to either the EoP group or the control group. Randomization was carried out by the first authors by means of concealed envelopes containing the name of the group. Group allocation was then reported by mail to the physiotherapist and the patient. Randomization was stratified according to diagnosis (cardiovascular diseases, metabolic syndrome, type II diabetes, and other diseases) in order to distribute diagnosis groups evenly in the two groups.

### Outcome measures

The EoP physiotherapists carried out both the physiological and patient-reported measures. Changes in physiological measures (VO_2_max, bodyweight, BMI, and HbA1c) and patient-reported measures (physical activity, health-related quality of life, amount and intensity of exercise, compliance with national guidelines for physical activity, and self-reported physical fitness) were assessed at the time of the health profiles (Figure 1).

*Maximal oxygen uptake (VO_2_max) *was measured using a maximal indirect cycle ergometer test modified from Pedersen & Nielsen [21], where VO_2_max was calculated from the maximal work capacity (Wmax). All tests were completed on a mechanically braked cycle ergometer (Ergomedic 874E or 828E, Monark, Varberg, Sweden). Rate of perceived exertion was evaluated using the 6–20 point Borg scale [22]. Heart rate was measured using a telemetric system (Polar Vantage NV, Polar Electro KY, Kempele, Finland). Each workload consisted of three minutes of cycling at 60 rpm. A choice of two protocols was available: 1) an initial workload of 30 watts and increments of 30 watts until exhaustion (classic protocol), 2) an initial workload of 30 watts and increments of 60 watts until the subject rated perceived exertion ≥ 13 (somewhat hard). Thereafter increments of 30 watts were used until exhaustion (progressive protocol). The test was continued until the subject was unable to maintain a pedal frequency of 60 rpm despite verbal encouragement. Workload, maximal heart rate and total time were recorded, and Wmax and VO_2_max were calculated.

*Glycosylated hemoglobin (HbA1c) *was measured in capillary blood using the DCA 2000+ (Bayer Diagnostics Europe Ltd., Dublin, Ireland), and was only assessed in patients with reduced insulin sensitivity. HbA1c is an indicator of mean blood glucose level over the last 8–12 weeks and indirectly a measure of glycemic control [23]. In a comparison between DCA 2000+ and the gold-standard technique in HbA1c assessment the correlation was above 0.9, and the test-retest reliability with the DCA 2000+ was above 95 % [24,25].

*Bodyweight *was measured prior to the cycle ergometer test with patients wearing light clothes and no shoes using a commercial scale.

*Body Mass Index (BMI) *was calculated by dividing bodyweight with height squared.

All patient-reported measures were assessed by means of self-administered questionnaires distributed by the EoP physiotherapist during the health profiles. The questionnaire was self-explanatory, easy to fill in, not too extensive, and consisted of preset response categories.

*Physical activity *was assessed using a short questionnaire, which allowed for conversion to MET values [26].

*Health-related quality of life *was assessed using both the SF-12v2 [27] and EQ-5D [28].

*Amount and intensity of exercise *were assessed by asking 'how much exercise do you do during an average week?', and 'at what intensity do you most often exercise?'

*Compliance with national guidelines for physical activity *was assessed by asking 'how many days during an average week are you physically active more than 30 minutes?'

*Self-reported physical fitness *was assessed by asking 'how do you rate your present physical fitness?', 'how do you rate your present physical fitness compared to four months ago?', and 'how do you rate your present physical fitness compared to people your age?'

The outcome measures are surrogate measures for reduction in risk of morbidity and mortality.

All physiotherapists were trained in the different aspects of the evaluation prior to initiating the randomized trial. A manual described all parts of the evaluation in detail, and each clinic was visited several times before and during the evaluation.

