### Statistical analysis

The changes from 0–4 and 0–10 months within the two groups separately will be assessed using paired t-test or Wilcoxon rank sum test depending on distribution. Furthermore, boxplots will be made for delta values for the changes from 0–4 and 0–10 months.

Comparisons between the EoP group and the control group will be made with changes from 0–4 and 0–10 months. The analysis will be performed as an intention-to-treat and carried out using a regression model incorporating delta values, controlling for baseline values, and adjusted for the effect of the different centres (physiotherapist clinics), further robust variance will be applied. For variables not fulfilling the normal distribution of residuals a Wilcoxon rank sum test will be used on delta values. These analyses will be supplemented with 'per protocol analyses'.

Drop-out analyses will be carried out for 0–4 months and 4–10 months. Completers and non-completers will then be compared for the different baseline variables using boxplots. The effect of drop-out will be compared with differences between the EoP group and the control group.

Statistical significance was set at p < 0.05.

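### One fitness item already rates change over the past four months, so at ten months it covers only months 6–10 and cannot serve as change since baseline

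*Protocol article*

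**What the plan says.** The Outcome measures section of the protocol article builds self-reported physical fitness from three questions. Two are status ratings: fitness now, and fitness relative to people of the same age. The third asks "how do you rate your present physical fitness compared to four months ago".

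The same section lists changes in the patient-reported measures among the outcomes and names this one: "compliance with national guidelines for physical activity, and self-reported physical fitness) were assessed at the time of the health profiles". The abstract and the Statistical analysis section use baseline, four months and ten months for the group comparison.

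The Statistical analysis section sets one rule for all outcomes:
- Within groups: "The changes from 0–4 and 0–10 months within the two groups separately will be assessed using paired t-test or Wilcoxon rank sum test", with boxplots of the differences.
- Between groups: "Comparisons between the EoP group and the control group will be made with changes from 0–4 and 0–10 months", using "a regression model incorporating delta values, controlling for baseline values" and adjusting for clinic.
- Fallback when residuals are not normal: a rank test on the differences. No baseline adjustment is stated for it.

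No section exempts the third fitness question, says that its raw answer will be analysed, or changes its reference period at ten months.

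**The concern.** A question that asks about the last four months measures a different stretch of time at each visit. At baseline it describes the four months before the trial, at month 4 the training period, and at month 10 the period from month 6 onwards. Subtracting the baseline answer therefore does not give change in fitness since baseline.

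The ten-month comparison is one of the trial's stated aims. The programme ends at about month 4, so the long-term question is whether its gain is kept. On this item, a patient who improved and held the improvement should truthfully answer that nothing has changed. Taken at face value, the result would count against the programme exactly where the programme had worked.

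**Working it through.** **Inputs.** The item wording and its four-month look-back come from Outcome measures. The comparison times (0, 4 and 10 months) and the difference rule come from Statistical analysis. The 16-week length of the programme comes from the abstract. The fitness paths below are assumed, in arbitrary units, because the article gives no data for this item.

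**The plan's own figure.** The only design figure is 22 per group, for VO2max. It reproduces: 15% of 20 is 3, the SD is 3, and 2 × (1.96 + 1.282)² × 3²/3² = 21.02, rounded up to 22 (two-sided 0.05, power 0.9). It has no bearing on this item.

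**What the item measures.** Let F(t) be fitness at month t. An accurate answer at month t is X(t) = F(t) − F(t−4). The planned differences are then:
- 0–4: X(4) − X(0) = [F(4) − F(0)] − [F(0) − F(−4)]
- 0–10: X(10) − X(0) = [F(10) − F(6)] − [F(0) − F(−4)]

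Change since baseline would be F(4) − F(0) and F(10) − F(0). In the 0–10 expression, change over months 0–6 has dropped out, and those months contain the whole supervised programme.

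**Illustrations.**

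| Assumed path | True change 0–4 / 0–10 | Answers at 0 / 4 / 10 | Difference 0–4 / 0–10 |
|---|---|---|---|
| A. Flat before, gain of 1 by month 4, kept | 1 / 1 | 0 / 1 / 0 | 1 / 0 |
| B. As A, half lost evenly over months 4–10 | 1 / 0.5 | 0 / 1 / −0.33 | 1 / −0.33 |
| C. Flat throughout | 0 / 0 | 0 / 0 / 0 | 0 / 0 |
| D. Fell by 1 before referral, then flat | 0 / 0 | −1 / 0 / 0 | 1 / 1 |
| E. Fell by 1 before referral, gain of 1 by month 4, kept | 1 / 1 | −1 / 1 / 0 | 2 / 1 |

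In row B, F(6) = 1 − 0.5 × 2/6 = 0.833 and F(10) = 0.5, so X(10) = 0.5 − 0.833 = −0.33.

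**Between groups at ten months.** A trained patient on path A against a control on path C shows 0 − 0 = 0, where the truth is 1. Path B against C shows −0.33, where the truth is +0.5. Path E against D shows 1 − 1 = 0, where the truth is 1.

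**Between groups at four months, regression.** Write the planned model as X(4) − X(0) = a + b·group + c·X(0) + error, leaving out the clinic terms, which do not alter the argument. Moving X(0) across gives X(4) = a + b·group + (c + 1)·X(0) + error. The group coefficient b and the residuals are identical to those from the raw four-month rating adjusted for baseline. That rating covers months 0–4, so the contrast is sound. The same identity holds at ten months, but there X(10) itself covers the wrong months, so it does not help.

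**Within groups, and the rank-test fallback.** No such cancellation occurs here. Path D shows an apparent improvement of 1 at both visits in a patient whose fitness has not moved since baseline. In the unadjusted rank test between arms, randomisation balances the pre-trial rating on average (E against D at four months: 2 − 1 = 1, as it should be). Even so, the quantity being ranked is not change since baseline.

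**The case against.** Three things can fairly be said against the point.

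First, the difference rule is general, in a condensed article, and no sentence says that this item's answers will be subtracted from each other. How a single question is scored could be settled in an analysis plan or manual that is not shown. This limits certainty about what will be done. It does not remove the mismatch in what is written, because the article names changes in self-reported physical fitness among the outcomes, defines that outcome partly by this question, and makes no exception.

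Second, a four-month look-back fits the month-4 visit exactly, and the main regression controls for baseline. This objection stands in full for the four-month regression. A reader might infer that subtracting the baseline answer inflates the variance of that comparison and so shrinks the effective sample below 22 per group. The documents do not support this. The adjusted model gives the same coefficient and residuals as the raw rating, the 22 was calculated for VO2max, and no SD or correlation is given for this item.

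Third, the item matters little: it is one of three questions within one of several patient-reported measures, and the other two are status ratings that can carry change since baseline. That is correct, and it bounds the consequence.

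**Conclusion.** The point holds in a limited form. At ten months the item covers only months 6–10 under every planned analysis, so a gain that is kept reads as no change. At four months the fault lies in the paired tests, the boxplots of differences and the unadjusted rank-test fallback, and not in the baseline-adjusted regression. The fallback is a realistic route, since the questionnaire uses preset response categories.

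A reader might infer that a fully maintained benefit would come out reversed. It would not: full maintenance gives a null. A wrong sign needs a further assumption, such as partial loss of the gain after month 4 (the −0.33 against +0.5 illustration) or late improvement among controls.

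The conclusion assumes that the question is put in the same words at each visit and that patients answer for the period it names. The sizes shown are illustrations, not estimates. The VO2max result, which sized the trial, is unaffected.

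**What to change.** Add one sentence to the Statistical analysis section that takes this item out of the analyses of differences, including the paired tests and boxplots. At four months, compare the rating itself between arms, by the baseline-adjusted regression or by a rank test on the raw rating. At ten months, either leave the item out of the 0–10 comparison or report it openly as perceived change over months 6–10. Keep the other two fitness questions in the difference analyses.

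The cost is that one sentence. The analysis is described in the future tense, so it can still be changed. Rewording the month-10 question to refer to trial entry would also repair it, but only for questionnaires not yet given. That is doubtful, because the article describes the trial as conducted in 2005–2006.

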### Sample size

Power calculations were performed for expected changes in VO_2_max. VO_2_max at baseline was estimated to 20 ml O_2_*(min*kg)^-1^, expected improvements were 15%, and expected SD was 3 ml O_2_*(min*kg)^-1^. Alpha was set at 0.05 and a power of 0.9 was chosen. Using these assumptions in the 'sampsi' command in Stata 9.0 the sample size was estimated to 22 in each group.

### Statistical analysis

The changes from 0–4 and 0–10 months within the two groups separately will be assessed using paired t-test or Wilcoxon rank sum test depending on distribution. Furthermore, boxplots will be made for delta values for the changes from 0–4 and 0–10 months.

Comparisons between the EoP group and the control group will be made with changes from 0–4 and 0–10 months. The analysis will be performed as an intention-to-treat and carried out using a regression model incorporating delta values, controlling for baseline values, and adjusted for the effect of the different centres (physiotherapist clinics), further robust variance will be applied. For variables not fulfilling the normal distribution of residuals a Wilcoxon rank sum test will be used on delta values. These analyses will be supplemented with 'per protocol analyses'.

Drop-out analyses will be carried out for 0–4 months and 4–10 months. Completers and non-completers will then be compared for the different baseline variables using boxplots. The effect of drop-out will be compared with differences between the EoP group and the control group.

Statistical significance was set at p < 0.05.

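### The change-score comparison labelled intention-to-treat is, run as written, an available-case analysis by allocated arm, and the planned drop-out analyses leave its estimate unchanged

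*Protocol article*

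**What the plan says.** All the relevant text is in the protocol article under Statistical analysis.

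- Contrasts: "Comparisons between the EoP group and the control group will be made with changes from 0–4 and 0–10 months".
- Label and estimator: "The analysis will be performed as an intention-to-treat and carried out using a regression model incorporating delta values, controlling for baseline values". The model also adjusts for centre and uses robust variance.
- Fallback where residuals are not normal: "a Wilcoxon rank sum test will be used on delta values".
- Supplement: "These analyses will be supplemented with 'per protocol analyses".
- Drop-out: "Drop-out analyses will be carried out for 0–4 months and 4–10 months". Then: "Completers and non-completers will then be compared for the different baseline variables using boxplots". Finally: "The effect of drop-out will be compared with differences between the EoP group and the control group".

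The section does not say how a patient without a 4- or 10-month value enters the comparison. It names neither imputation nor a repeated-measures model, and it does not expressly restrict the analysis to patients with both visits.

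**The concern.** The section fixes three things: a label (intention-to-treat), an estimator (separate analyses of the 0–4 and 0–10 month deltas) and a response to drop-out. The estimator does not deliver what the label promises. A delta is undefined when the follow-up value is absent, and adjusting for baseline and centre does not bring that patient back. The rank test works on the same deltas and has the same limitation.

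The plan expects non-completers and classifies them, but nothing it states brings them into the estimate. The boxplots are descriptive. The comparison of the effect of drop-out with the group difference has no stated method and does not feed back into the regression.

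The design gives reason for care. Under Outcome measures, outcomes are taken at the health profiles by the EoP physiotherapists, and under Intervention those profiles are part of the programme. A patient who leaves the programme altogether may therefore lose the outcome too. Patient and physiotherapist both know the allocation, and controls are offered EoP after the evaluation, so reasons for leaving could plausibly differ between arms. A reader who trusts the label would take the estimate as applying to everyone randomised.

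**Working it through.** **1. The plan's own figure.** Inputs from Sample size: baseline VO2max 20 ml/(min·kg); "expected improvements were 15" per cent, so Δ = 0.15 × 20 = 3; SD 3; alpha 0.05; power 0.90. The two-sided normal formula gives n = 2 × (SD/Δ)² × (1.960 + 1.282)² = 21.01 with unrounded quantiles, rounded up to 22 per group. The stated 22 is reproduced. The point below does not depend on it, except that Δ = 3 sets the scale.

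**2. Who enters each contrast when deltas are analysed without imputation.**

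| Measured at (months) | 0–4 contrast | 0–10 contrast |
|---|---|---|
| 0, 4, 10 | in | in |
| 0, 4 | in | out; 4-month value unused |
| 0, 10 | out | in |
| 0 only | out | out |

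Patients who are measured stay in their allocated arm whatever their adherence. The 0–4 contrast keeps patients lost afterwards. The set is therefore available-case, visit by visit.

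**3. Illustration of size (assumptions, not plan figures).** Let a fraction d of EoP patients have no outcome and a mean gain m relative to control. Let observed EoP patients gain 3.0 relative to control, and let control losses leave the control mean unchanged. The delta regression then estimates 3.0, while the effect in all randomised patients is (1 − d) × 3.0 + d × m.

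| d | m = 0 | gap from 3.0 | m = 1.5 (half the gain) | gap from 3.0 |
|---|---|---|---|---|
| 10% | 0.9 × 3.0 = 2.70 | 0.30 | 2.70 + 0.15 = 2.85 | 0.15 |
| 20% | 0.8 × 3.0 = 2.40 | 0.60 | 2.40 + 0.30 = 2.70 | 0.30 |
| 30% | 0.7 × 3.0 = 2.10 | 0.90 | 2.10 + 0.45 = 2.55 | 0.45 |

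**4. Precision, on the same assumed rates in both arms.** Power = Φ(Δ / (SD × √(2/n)) − 1.960). At n = 22 it is 0.91. At n = 19.8, 17.6 and 15.4 (10, 20 and 30% lost) it is 0.88, 0.84 and 0.79.

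**5. What a repeated-measures model recovers.** It uses the second and third rows of the table in step 2 for both contrasts, but not the fourth row. If every drop-out in step 3 has only a baseline value, such a model also returns about 3.0. If those EoP patients are instead given the control arm's mean change, and controls change by 0, the result at d = 20% is 0.8 × 3.0 + 0.2 × 0 = 2.4. The repeated-measures model alone is therefore not enough, and the sensitivity analysis is needed as well.

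**The case against.** The strongest reply is that this is a condensed article. Handling of missing outcomes is commonly left to a full protocol or analysis plan, and its absence here is no error. A change-score regression can include everyone randomised once missing values are imputed, and the text does not exclude that. Nor does stopping training mean missing a measurement: the health profiles are separate from the training sessions. A patient who stops training but attends at 4 and 10 months is analysed as randomised, which is an ordinary meaning of intention-to-treat and is distinct from the per-protocol analyses named separately.

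Most of this stands, and it limits the point. A reader might infer that the plan can only yield a completers' analysis. The documents do not support that: imputation is neither planned nor ruled out, and without it the analysis is available-case by allocated arm. A reader might infer that boxplots are the only response to drop-out. They are not, because a comparison of the effect of drop-out with the group difference is also planned, although without a method. A reader might infer that the result would favour EoP by some 25% (3.0/2.4 = 1.25). That ratio needs 20% EoP drop-out, no gain in any of those patients and no effect of control drop-out. None of these is in the documents, and informative control drop-out could move the estimate either way.

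The reply does not remove the mismatch between the stated label and the stated estimator. It also does not explain why the 10-month contrast should ignore 4-month data already collected.

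**Conclusion.** The point holds in limited form and is worth acting on. Followed as written, each contrast omits randomised patients who lack that visit, and the 10-month contrast discards 4-month values from patients lost later. The planned drop-out analyses leave the estimate unchanged. The intention-to-treat label therefore needs a stated rule for missing outcomes, or a qualification.

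The size and direction of any bias are unknown, because no drop-out rate is given. Under the assumptions in the working, the gap is 0.3 to 0.9 ml/(min·kg) for 10 to 30% EoP drop-out with no gain, and 0.15 to 0.45 if drop-outs keep half the gain. These figures show scale only and do not predict this trial's result.

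**What to change.** 1. For the continuous outcomes, analyse the 4- and 10-month values in one repeated-measures model with arm-by-visit terms and baseline, keeping the planned centre adjustment and robust variance. Read both contrasts from it.
2. Add a sensitivity analysis covering all randomised patients, including those with no follow-up value, in which missing EoP changes are given the control arm's mean change. Use multiple imputation, so that the standard error is not understated.
3. Show drop-out, and the comparison of completers with non-completers, by arm.
4. Describe any analysis left on observed deltas, including the rank-test fallback, as available-case rather than intention-to-treat.

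The cost is a change of wording and modest programming, with no change to trial conduct. The main model assumes that outcomes are missing at random, and it still omits patients with no follow-up value. The sensitivity analysis addresses both limits.
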